## Methods and analysis

### Study type/study design

Decide TB is a pragmatic cluster-randomised trial (2024–2026) with a stepped wedge and hybrid effectiveness-implementation trial type 2 design. It will evaluate a comprehensive TDA-based approach (intervention) versus the SOC (control) for screening, diagnosis and treatment decision for childhood TB (see figure 1).^23^ Districts in each country will be randomly selected to successively initiate the intervention every quarter. Prior to the trial, a site selection survey will systematically identify districts and facilities that have the capacity to deploy TDAs and present a diversity of health systems and geographical characteristics.^24^ Formative research will describe the local facilities and community dynamics to highlight potential implementation barriers and facilitators and inform on intervention implementation strategies. The intervention will be implemented by the NTPs of Mozambique and Zambia. The effectiveness of the intervention in terms of TB case detection (children started on TB treatment) among children attending care will be assessed by comparing it to the SOC using both aggregated and register-based individual routine health data from the Ministry of Health (MoH). Additionally, aggregated and register-based individual data will be collected retrospectively for 12 months for secondary effectiveness endpoints (table 1). We will develop an electronic medical record (EMR) to collect individual health data among all children with presumptive TB. The EMR will be developed in Demographic Health Information System 2 (DHIS2) using the same variables for both countries. The diagnostic accuracy of the SOC and of the intervention will be assessed in an additional district in each country not participating in the stepped wedge design. The acceptability, feasibility, health economics and health policy evaluations of the intervention and of its implementation will be nested within the trial and use repeated mixed method surveys (in a convergent design). The study will start with formative research in February 2024. The stepped wedge trial will start mid-2024 and end mid-2026. The last children enrolled during the trial will be followed up until the end of 2026. A post-intervention sustainability survey will take place early 2027. Both countries will be autonomous in terms of trial start date and analysis.

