### Study settings

The study will be conducted in Mozambique and Zambia, two high TB burden countries with overall estimated TB incidences of 361 and 283 cases per 100 000, respectively.^36^ The stepped-wedge trial will be implemented in four districts in each country, each composed of one DH and six PHCs; the additional district (not randomised) will be composed of one DH and three to four PHCs. The estimated number of children attending outpatient department (OPD) in each district per quarter is 10 500, including 3500 at the DH level and 7000 children at the PHC level.

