### Sample size

For the effectiveness component, the statistical power to detect an increase in TB detection among children attending care (primary effectiveness endpoint) was estimated to be 0.922 for country and 0.981 for joint-analyses, using the Shiny CRT Calculator^37^ and using the following assumptions: (1) an estimated attendance of 10 500 children per quarter and per district (3000 at DH and 7500 at PHC levels); (2) a hypothesised 0.1% TB case detection rate among sick children attending care at SOC phase and 0.3% at intervention phase; (3) a discrete time decay correlation structure with a cluster auto-correlation of 0.95; (4) an intra-class correlation of 0.03 adjusted to the low prevalence of a rare binary outcome^38 39^; (4) a significance level of 5%; (5) a T-distribution applied as small sample correction for CI estimation.

Sample sizes for the acceptability, feasibility/implementation, health economics and health policy evaluations were determined as follows: (1) for HCWs (per district)—an exhaustive recruitment estimated at ~200 HCWs for the child TB and TB diagnosis questionnaires (table 1); 15 HCWs per district using digital tools for the usability questionnaire; a purposive selection of ~eight HCWs for individual interviews and of 12 HCWs per district for the time and motion study; (2) for parents/caregivers (per district): a purposive selection of 8–12 parents/caregivers for group interviews during the formative survey; of ~eight dyads (parent/caregivers-child) for individual qualitative interviews during the trial; of 240 parents/caregivers per country for patient cost surveys; (3) for key informants: a purposive selection of 5–10 stakeholders at district level and of 2–5 at provincial, national and international levels, respectively, per country.

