### Endpoints

The endpoints of the different research components will be quantitative (box 1), qualitative or mixed.

Box 1Trial interdisciplinary quantitative endpoints.Effectiveness endpointsPrimary endpoint: proportion of children started on treatment for tuberculosis (TB) among sick children attending care at participant health facilities for any health complaints.Proportion of children treated for TB among those with presumptive TB, including children with microbiologically confirmed TB.Proportion of children from high-risk groups treated for TB (age <2 years, children living with HIV, children with severe acute malnutrition) among all children from high-risk group attending care and among children from high-risk groups with presumptive TB.Proportion of children with TB who are microbiologically confirmed (ie, smear or Xpert or lipoarabinomannan positive), ratio of <5 years to 5–14 years among children with TB and ratio of pulmonary TB to extrapulmonary TB.Time from presumptive TB identification to final TB treatment decision and access to TB diagnostic assessment defined as the proportion of children with presumptive TB having completed assessment with the treatment decision algorithms (TDAs) and clinical decision support systemClinical Decision Support Systems, including in high-risk groups.Concordance of the TDA result and the final TB treatment decision using the proportion of children wrongly initiated or not initiated on TB treatment defined as: (1) children not started on TB treatment despite positive score; (2) children initiated on TB treatment despite negative score.Proportion of missed TB cases and over-diagnosed TB cases (unlikely TB with a positive score) compared to a reference standard diagnosis. This will be assessed in a subset of children with full diagnostic assessment (≥1 respiratory or stool sample tested with Xpert MTB/RIF Ultra, chest X-ray (CXR) availability, clinical evaluation and follow up) at district hospital or with access to CXR.Concordance of the severity evaluation and decision for short TB treatment regimen using the proportion of (1) children with 4-month TB treatment regimen used despite severe disease as assessed by the clinical/CXR evaluation; (2) children with 6-month TB treatment regimen despite non-severe disease as assessed by the clinical/CXR evaluation.Proportion of missed severe TB cases and cases over-diagnosed as severe, compared to reference standard severity assessment by expert at low level of health care: (1) children with non-severe disease according to clinical criteria despite severe disease as evaluated by expert CXR read; (2) children with clinically assessed severe disease despite non-severe disease as evaluated by expert CXR read.Proportion of children with presumptive TB and with non-severe TB disease initiated on shorter TB treatment.TB treatment outcomes as defined per WHO (treatment success, cured, treatment completion, loss to follow-up, death, treatment failure) overall and stratified by severity and regimen duration.Deaths averted assessed through modelling.Number of adults with TB, including microbiologically confirmed TB, and proportion of all TB diagnosed that is child TB.Acceptability endpointsCo-primary endpoints: clinicians stating that in their facility they are confident in their ability to decide to initiate TB treatment in a child <5 years/in a child 5–14 years.Secondary endpoint: clinicians stating that in their facility they are confident in their ability to decide to initiate TB treatment in a child.Secondary endpoints: clinicians stating that in their facility they are not over-diagnosing children <5 years/5–14 years/all children, that is, initiating children on TB treatment when they actually do not have TB.Secondary endpoints: clinicians stating that in their facility they are supporting children <5 years/5–14 years/all children with TB to access care/medication as swiftly as they should.Feasibility and implementation endpointsCo-primary endpoint: healthcare workers (HCWs) stating that in their facility they have the adequate tools to diagnose children <5 years for TB/5–14 years for TB*.Secondary endpoint: HCWs stating that in their facility they have the adequate tools to diagnose any children (<15 years) for TB*.Secondary endpoint: clinicians stating that in the last 3 months they started a child on TB treatment.Health economics endpointsa. Cost analyses of the standard of care (SOC) and of the comprehensive TDA-based approachTotal TB care costs from the health system perspective.Unit cost per TB care activity (eg, clinical assessment, CXR).Total TB care costs of overdiagnosis (false positive)—intervention only.Total costs incurred by parents/caregivers for receiving child TB care.b. Cost-effectiveness of the comprehensive TDA-based approach compared to the SOC:Modelled health impact measure:Number of children treated for TB.Number of adults treated for TB.Number of deaths.Disability-adjusted life years (DALYs): measure of healthy life lost, either through premature death or living with disability due to illness.Cost-effectiveness measure, that is, incremental cost per:Incremental number of children treated for TB.Death averted.DALY averted.c. Budget impact of the comprehensive TDA-based approach scale-up compared to the SOC over 5 years:Cost of scaling up the comprehensive TDA-based approach nationally.Cumulative number of children and adults treated for TB, lives saved and DALYs averted during a 5-year scale-up.

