#### Effectiveness endpoints

For the effectiveness endpoints, data will be analysed both at trial (joint analysis) and country levels (country analysis). The primary effectiveness analysis will focus on the stepped-wedge period (five quarters) and compare all endpoints using aggregated or individual register-based data between SOC and intervention. Generalised estimating equations^40^ with fixed effects for steps and intervention will be used. Data from the transition period will be removed. We will conclude that the intervention is more effective than the control if the observed difference in outcome is statistically significant (p<0.05). Model goodness-of-fit will be assessed, and alternative solutions will be discussed and considered, if relevant. Sensitivity analysis will use the same approach but will consider data from the transition period as intervention data. Secondary analysis will be planned and performed on all districts to (1) assess TDA-based approach effectiveness on diagnostic accuracy and implementation and (2) account for secular trend and potential bias of the study effect. Subgroup analyses will be performed considering the type of vulnerability (including age group), sex, facility-level and country. Analyses will be carried out with R V.4.4 or higher.

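### If treatment outcomes among treated children are compared between phases, a difference in either direction can come from case mix alone, and the planned severity strata cannot correct it

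*Protocol article*

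**What the plan says.** - **Endpoint.** Box 1 (Endpoints) lists WHO treatment outcomes among the effectiveness endpoints: "treatment success, cured, treatment completion, loss to follow-up, death, treatment failure) overall and stratified by severity and regimen duration". No denominator is written out, but these outcomes are defined only for children who started treatment.
- **Comparison.** Under Data analysis, Effectiveness endpoints: "The primary effectiveness analysis will focus on the stepped-wedge period (five quarters"), and that analysis will "compare all endpoints using aggregated or individual register-based data between SOC and intervention". The intervention is then to be judged "more effective than the control if the observed difference in outcome is statistically significant (p<0.05"). The sentence does not restrict this rule to the primary endpoint.
- **Expected change in who is treated.** Sample size assumes "a hypothesised 0.1% TB case detection rate among sick children attending care at SOC phase and 0.3% at intervention phase".
- **Data sources.** In Table 1, the TB treatment registers cover the retrospective, SOC, intervention and follow-up periods, but no register variables are listed. Treatment outcomes, severity assessment and treatment duration are named only in the EMR row. The EMR is used in the intervention phase and, under SOC, only in the additional non-randomised district.
- **Retrospective data.** Study type/study design adds 12 months of retrospective aggregated and register data for secondary effectiveness endpoints.
- **Follow-up.** The same section states: "The last children enrolled during the trial will be followed up until the end of 2026".

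**The concern.** Being treated is the primary outcome, so the group of treated children is itself a product of the intervention. Comparing success or case fatality within that group conditions on something that happens after the switch. Randomising the order in which districts switch does not protect such a comparison: the SOC-phase and intervention-phase groups differ in composition even when attenders are comparable.

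What is at stake is the observed patient-outcome evidence. Box 1 assesses deaths averted by modelling only, and the Discussion expects the results to inform national and WHO policy. A significant difference in success or case fatality could be reported as effectiveness, or as harm, when it reflects only who was added.

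The regimen strata raise a related problem. In the plan's approach severity determines regimen, so the 4-month and 6-month groups differ by design, and their outcome windows may differ in length.

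**Working it through.** **Figures from the plan.** Treatment starts are 0.1% and 0.3% of attenders. Attendance is "an estimated attendance of 10 500 children per quarter and per district". "The stepped-wedge trial will be implemented in four districts in each country", over five quarters. The power figures in Sample size concern the primary endpoint; none is given for treatment outcomes, and nothing below depends on them.

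**1. Composition of the treated group.**
- Ratio: 0.3 / 0.1 = 3. Share additional: (0.3 − 0.1) / 0.3 = 2/3. This assumes comparable attenders and that children treated under SOC would also be treated under the intervention.
- With one district switching each quarter, SOC has 1+2+3+4 = 10 district-quarters per country and the intervention 4+3+2+1 = 10.
- SOC: 10 × 10 500 × 0.001 = 105 treated. Intervention: 10 × 10 500 × 0.003 = 315. Removing one transition month per district leaves (10 − 4/3) × 31.5 = 273.

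**2. Who the added children might be.** The Introduction gives algorithms A and B sensitivities of 86% and 84% and specificities of 37% and 30%. With an assumed TB prevalence of 10% to 30% among children assessed, the positive predictive value is 13% to 37% for A and 12% to 34% for B. For example, A at 10%: 0.086 / (0.086 + 0.63 × 0.9) = 0.132. Added children with mild or no TB are therefore plausible. So are sicker ones: the intervention brings dedicated algorithms for children living with HIV and those hospitalised with SAM, and the Introduction says children with HIV or SAM are at higher risk of dying from TB.

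**3. Case mix alone, no child's outcome changed (risks assumed).** Intervention-phase success = s0/3 + 2·s1/3, where s0 is success in SOC-type children and s1 in added children.
- s0 = 80%, s1 = 95%: 26.7 + 63.3 = 90.0%, a change of +10.0 points.
- s0 = 85%, s1 = 95%: 28.3 + 63.3 = 91.7%, +6.7 points.
- s0 from 75% to 90% with s1 from 90% to 98%: 0 to +15.3 points.
- Reverse case, s0 = 85%, s1 = 75%: 28.3 + 50.0 = 78.3%, −6.7 points.
- Case fatality of 8% in SOC-type children and none in added children: 8.0% falls to 8/3 = 2.7%. Starting from 4% or 12%, it falls to 1.3% or 4.0%.

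**4. Could this reach p<0.05?** A simple two-proportion comparison of 80% with 90% has power 0.74 per country (105 vs 315) and 0.95 jointly (210 vs 630). This ignores clustering and keeps the transition month, so it shows only that the artefact is not negligible.

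**5. Would a per-attender denominator cure it?** Not in general.
- Deaths on treatment per 10 500 attenders: SOC 10 500 × 0.001 × 0.08 = 0.84. If no added child dies, it stays at 0.84.
- If added children die at 2%: 0.84 + 10 500 × 0.002 × 0.02 = 1.26. The count rises even if those children would have died more often untreated, because deaths in untreated children are not counted.
- Successes: 10.5 × 0.80 = 8.4 against 31.5 × 0.90 = 28.4, driven mainly by treatment starts.

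**6. Regimen strata.** At an assumed constant monthly risk h of death or loss, cumulative risk is 1 − (1 − h)^m. For h = 1%: 3.9% at 4 months, 5.9% at 6. For h = 3%: 11.5% and 16.7%. Unequal windows alone would give about 2 to 5 points between strata. If 30% to 70% of children were on the shorter window, the overall success proportion would shift by 0.6 to 3.7 points.

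**The case against.** The strongest reply is that the plan never says in terms that treatment outcomes are compared between phases. Table 1 names them only in the EMR row, and Data collection and tools assigns EMR data to endpoints collected at the intervention phase. A description within the intervention phase is therefore possible. This stands, and it is why the point is conditional. But the article does not state that reading. Treatment registers span both phases, and the analysis sentence covers all endpoints using register data.

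The p<0.05 sentence might be meant for the primary endpoint alone. It does not say so.

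The endpoint is already stratified by severity and regimen. That helps within the intervention phase. It does not help between phases: no SOC severity assessment is described for the randomised districts, and SOC in Mozambique is said to include no CXR.

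The SAP may settle this, since the article defers analysis detail to it. Denominators could indeed wait. The broad comparison and the unrestricted rule, however, are fixed in the article itself.

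A reader might go further than the documents allow:
- That success will rise and flatter the intervention. The direction depends on who is added, and added children who truly have TB may benefit.
- That the switch moves children from 6 to 4 months. The SOC section gives no regimen duration.
- That observation closes at month 4 and hides later harm. Nothing says so. The EMR includes status at a follow-up visit, and the last children are followed to the end of 2026.

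**Conclusion.** The concern holds conditionally. If register-based treatment outcomes are compared between SOC and intervention, as the analysis section most naturally reads, the comparison conditions on treatment start. The intervention is designed to change that, with about two thirds of intervention-phase treated children additional on the plan's own rates. A difference in success or case fatality can then arise in either direction with no child's outcome altered, and the severity strata have no documented SOC counterpart with which to adjust.

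Only the tripling and the two-thirds share follow from the plan's figures, the latter under the assumptions in step 1. The shifts of 0 to +15.3 points, the −6.7 point reverse case and the 2 to 5 point window effect rest on assumed risks and illustrate scale. The documents do not show that the intervention will look better than it is, nor that harm from shorter treatment will go unseen. The primary endpoint is unaffected.

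**What to change.** 1. State whether treatment outcomes are compared between phases and from which source. State that outcomes among treated children are descriptive and not subject to the p<0.05 rule.
2. Add, as a sensitivity analysis, the between-phase comparison restricted to microbiologically confirmed TB. Note that numbers will be small and that it is not fully phase-neutral if testing changes; for Mozambique, the intervention section lists more specimen types than the SOC section.
3. Show any count per attending child only as context, with the warning that on-treatment deaths and successes move with treatment starts and omit deaths in untreated children.
4. State that differences between the 4-month and 6-month strata will not be interpreted as a regimen effect. Where month-6 status is already in the register or EMR, report it for both groups. Follow-up from mid-2026 to the end of 2026 allows about six months for the last children, with little slack.

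Cost: wording in the analysis plan and no new data collection. The trial gives up a formal test of one secondary endpoint, the confirmed-TB comparison will be imprecise, and month-6 status will be missing for some children.

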**Figure 1 F1:**
[figure not shown]
Overall study design at the country level. SOC, standard of care; TDA, treatment decision algorithm.

**Table 1 T1:** Data collection and tools

	Site selection and formative research	Effectiveness	Acceptability	Implementation	Health economics	Health policy	Timing of data collection *Target population*	Data collected *Data collection method*
Aggregated data	X	X					Retrospective, SOC, intervention and follow-up *Children attending care, children with TB*	Aggregated health data routinely reported to the MoH in the national DHIS2 database including OPD attendance, number of children in high-risk groups, number of TB notifications in children, among others.
Individual data-based registers		X					Retrospective, SOC, intervention and follow-up *Children with presumptive TB and TB*	Data from presumptive TB registers and from TB treatment registers *Reported in created modules in DHIS2*
EMR		X					SOC in additional district only and intervention *Children with presumptive TB*	Demographics, clinical and anthropometric data, HIV status, radiological data and abdominal ultrasound examination, laboratory data, TDA used and score, TB severity assessment, TB treatment if initiated and duration, TB treatment outcomes, comorbidity management including antiretroviral treatment, nutrition therapy and status at follow-up visit *EMR data entry on tablet in DHIS2*
Child TB questionnaire	X		X	X			Formative phase and before end of trial *HCWs*	Knowledge, attitudes and practices of HCWs, their readiness to and their perceived feasibility of TDAs for childhood TB. *Self-administered REDCap questionnaire on tablet, with support from social sciences research assistants (SSRAs*).
TB diagnosis questionnaire			X	X			Quarterly (implementation and intervention) 6 monthly (acceptability) *HCWs*	Structured in three modules: (1) implementation module, to assess the scope of childhood TB diagnosis activity, barriers and facilitators and context; (2) acceptability module, to document perceptions of appropriateness of, utility of and self-confidence towards the diagnostic approach used in the facility; (3) intervention module (intervention arm only), to document the experience of the comprehensive TDA-based approach. *Self-administered REDCap questionnaire on tablet, with support from SSRAs*

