### Randomisation

In each country, health districts will be units of intervention and all will start the trial in the SOC arm. Randomisation will be done at the district level, separately for each country. For each district, the sequence will include SOC (3–12 months), intervention (3–12 months) with a lead-in/transition phase of 1 month for the stepped wedge part of the trial and then continued intervention in routine conditions with supervision (9 months) (figure 1). The randomisation list stratified by country will be generated by the trial statistician and will define the order in which each district will switch from control to intervention (every 3 months). The study coordinators will be blinded to the randomisation list and informed of the next district to switch 8 weeks prior to crossover.

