#### Acceptability, feasibility/implementation and health policy endpoints

Primary and secondary quantitative acceptability and feasibility endpoints (see table 1) will be analysed through the same stepped wedge trial analysis as for the primary effectiveness endpoint.

Rapid analysis methods will be used for the qualitative data collected right before and after the switch from control to intervention: the aim is to provide rapid feedback to implementers and key stakeholders at local and national levels and inform adaptation of implementation strategies to context. This analysis will be based on daily debriefs between social science research assistants and investigators, completion of a thematic matrix and summary of findings per implementation components. For the in-depth analysis of the qualitative data, a coding framework will be developed, based on themes predefined by the semistructured interview guides and emerging from the data as responsive to the acceptability, feasibility/implementation and health policy endpoints. Thematic summaries will be prepared for each endpoint, highlighting contextual specificities. Analyses will first be conducted country by country separately and then merged (and compared/contrasted when relevant) during finding consolidation and interpretation. Finally, quantitative and qualitative data will be combined and triangulated to assess certain acceptability, feasibility/implementation and health policy endpoints.

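### The 3-month recall of a secondary feasibility endpoint cannot fit into the two transition-free months of a district's first intervention quarter

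*Protocol article*

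**What the plan says.** Five statements in the protocol article meet on this endpoint.

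- **Endpoint** (Endpoints, Box 1, feasibility and implementation): "clinicians stating that in the last 3 months they started a child on TB treatment".
- **Steps and transition** (Randomisation): the list will "define the order in which each district will switch from control to intervention (every 3 months"), and the district sequence has "intervention (3–12 months) with a lead-in/transition phase of 1 month".
- **Length of the wedge** (Data analysis, Effectiveness endpoints): "The primary effectiveness analysis will focus on the stepped-wedge period (five quarters").
- **Handling of transition** (same section): "Data from the transition period will be removed". A sensitivity analysis counts those data as intervention instead.
- **Analysis of feasibility endpoints** (Data analysis, Acceptability, feasibility/implementation and health policy endpoints): they "will be analysed through the same stepped wedge trial analysis as for the primary effectiveness endpoint".

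Table 1 gives the timing of the TB diagnosis questionnaire as "Quarterly (implementation and intervention) 6 monthly (acceptability"). It names no date within the quarter. Linking the endpoint to this questionnaire is an inference. The other healthcare-worker survey that could carry the item, the child TB questionnaire, runs only in the formative phase and before the end of the trial, so it could not feed a stepped-wedge analysis.

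**The concern.** A yes/no answer about the past 3 months describes the 3 months before completion, not the day of completion. The recall is as long as a step, and the first month of a district's intervention time is set aside as transition. An answer given in that first quarter must therefore reach back into transition, and often further into SOC. A month cannot be cut out of a single yes/no answer, so dropping questionnaires by completion date does not deliver the removal that the analysis section asks for. Endpoints counted by calendar date do not have this difficulty.

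The error runs one way. Waves before the switch contain SOC time only, while first waves after it contain a mixture. If the intervention raises treatment starts, a first wave labelled as intervention understates it. A weak result on this item could then be read as poor uptake when part of it comes from the recall window.

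**Working it through.** **Inputs.** Recall 3 months (Box 1). Step 3 months and transition 1 month (Randomisation). Wedge of five quarters (Effectiveness endpoints). Four districts per country (Study settings). For the illustration only: 10 500 attendances per district-quarter, with detection of 0.1% in SOC and 0.3% in intervention (Sample size).

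**1. Calendar.** SOC/intervention months by district are 3/12, 6/9, 9/6 and 12/3. Each pair sums to 15 months, which reproduces the stated five quarters, so the transition month is not an extra month. The text attaches it to the intervention period, and the sensitivity analysis counts it as intervention. Both point to the first month after the switch. Intervention district-quarters per country are 4 + 3 + 2 + 1 = 10, of which 4 (40%) are first quarters. The fourth district has no other.

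**2. Content of the recall window.** For completion t months after the switch (0 < t ≤ 3): SOC = 3 − t, transition = min(t, 1), clean intervention = max(t − 1, 0).

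| t | SOC | Transition | Clean intervention |
|---|---|---|---|
| 1.0 | 2.0 | 1.0 | 0.0 |
| 1.5 | 1.5 | 1.0 | 0.5 |
| 2.0 | 1.0 | 1.0 | 1.0 |
| 2.5 | 0.5 | 1.0 | 1.5 |
| 3.0 | 0.0 | 1.0 | 2.0 |

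A fully clean window needs t − 3 ≥ 1, so t ≥ 4. The quarter ends at t = 3. A second intervention wave fielded in its first month would also still catch part of the transition month.

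**3. Other placements.** If the transition were the last SOC month or an added month, a survey on the final day would be clean. Every earlier date would still overlap the transition month.

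**4. Size, as an illustration.** Expected starts per district-quarter are 10 500 × 0.001 = 10.5 in SOC and 10 500 × 0.003 = 31.5 in intervention. Assume Poisson starts shared equally among n clinicians, so P(at least one start) = 1 − exp(−sum of monthly rates over the window). The value of n is an assumption, because the article gives only about 200 healthcare workers per district.

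For n = 40 the monthly rates are 10.5/40/3 = 0.0875 and 31.5/40/3 = 0.2625. The full contrast is [1 − exp(−0.7875)] − [1 − exp(−0.2625)] = 0.545 − 0.231 = 0.314.

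| Fielding | Transition rate | Sum of rates | P | Excess over SOC | Share of 0.314 |
|---|---|---|---|---|---|
| Quarter end, t = 3 | SOC | 0.6125 | 0.458 | 0.227 | 72% |
| Quarter end, t = 3 | halfway | 0.7000 | 0.503 | 0.273 | 87% |
| Quarter end, t = 3 | intervention | 0.7875 | 0.545 | 0.314 | 100% |
| Mid-quarter, t = 1.5 | SOC | 0.3500 | 0.295 | 0.064 | 21% |
| Mid-quarter, t = 1.5 | halfway | 0.4375 | 0.354 | 0.124 | 39% |

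Varying n:
- Transition at the SOC rate, n = 20 to 80: 70–77% at quarter end and 19–25% at mid-quarter.
- Transition halfway, n = 10 to 200: 84–94% and 35–57%.

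Together these give about 70–94% at quarter end and 19–57% at mid-quarter. Taking n to 200 at the SOC rate lowers the bottom slightly. The full contrast is then 0.1457 − 0.0511 = 0.0946, and the retained shares are (0.1153 − 0.0511)/0.0946 = 68% and (0.0676 − 0.0511)/0.0946 = 17%.

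**The case against.** The strongest reply is that most of the size is unknown. A quarterly item with a quarterly recall is naturally fielded at quarter end, where the window holds no SOC time. If the transition month already runs at the intervention rate, which the sensitivity analysis allows for, a quarter-end wave loses nothing. How a straddling answer is assigned to a period is ordinary content for the statistical analysis plan, which is not shown. The placement of the transition month would be confirmed by a figure that is also not shown. Finally, the percentages describe one wave, not the model estimate, and most intervention district-quarters (6 of 10) are not first waves.

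All of this limits the size, and it stands. It does not remove the conflict. Recall length, step length, transition and shared analysis are each fixed in the article. Under the placement that the text supports, even quarter-end fielding leaves one third of the window in transition. The sensitivity analysis relabels transition time but does nothing about SOC time in a window.

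A reader might infer more: that first-wave windows are mostly SOC time (50% SOC, 28% transition and 22% clean if completion is spread evenly over the quarter), or that the first wave shows only about a fifth of the effect. The documents do not support either as a finding. Even spread is stated nowhere. The one-fifth figure needs mid-quarter fielding, 40 clinicians and a transition month at the SOC rate, and none of these is stated. Nor does the article say outright that such answers are coded as full intervention exposure.

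**Conclusion.** The point holds in a limited form. As described, no fielding date in a district's first intervention quarter yields a 3-month recall window of clean intervention time. This concerns 4 of 10 intervention district-quarters per country, including the last district's only one, and removal by completion date cannot cure it.

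The expected bias is towards no difference. That direction assumes the intervention raises treatment starts and the transition month does not exceed the intervention rate. The first-wave contrast keeps about 70–94% at quarter end (up to 100% if transition runs at the intervention rate) and about 19–57% at mid-quarter, on the assumptions shown. The attenuation of the model estimate was not computed.

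This is one secondary, self-reported endpoint. A reader might infer a threat to the trial's main result, but the primary endpoint counts treatment starts from routine data, and the co-primary feasibility item has no stated recall window.

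**What to change.** **Fielding.** Ask the item in the last weeks of each quarter in all districts, so that little or no SOC time falls in an intervention window. This costs a scheduling instruction.

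**Analysis.** The wedge was due to start in mid-2024, so waves may already be in hand. Use completion dates to exclude first-wave answers whose window contains no clean intervention time (t ≤ 1). Then either code the remaining first-wave answers by the share of the window after transition, or report a sensitivity analysis that leaves out each district's first intervention wave. Share coding is an approximation, because a yes/no answer does not respond linearly to exposure. Leaving out the first wave removes 4 of 10 intervention district-quarters per country and leaves the last district with no intervention data on this endpoint, so it suits a sensitivity analysis better than the main one.

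**Item, if it can still be changed.** A recall of at most 2 months, asked at quarter end in all districts, avoids the overlap. On the n = 40 illustration the contrast becomes [1 − exp(−0.525)] − [1 − exp(−0.175)] = 0.408 − 0.161 = 0.248, or 79% of 0.314. A 1-month recall would give 0.231 − 0.084 = 0.147, or 47%, in every wave, which is a steep price for this problem. Changing the wording after waves have been collected would mix two definitions of the endpoint across calendar time. In that case the fielding and analysis changes are the safer course.
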